## Abstract

**Background:**

An anti-reflux catheter (ARC) may increase the tumor absorbed dose during radioembolization (RE) by elimination of particle reflux and its effects on hemodynamics. Since the catheter is fixed in a centro-luminal position, it may also increase the predictive accuracy of a scout dose administration before treatment. The purpose of the SIM trial is to compare the effects of ARC use during RE with holmium-166 (^166^Ho) microspheres in patients with colorectal liver metastases (CRLM), with the use of a standard end-hole microcatheter.

**Methods/Design:**

A within-patient randomized controlled trial (RCT) will be conducted in 25 patients with unresectable chemorefractory liver-dominant CRLM. Study participants will undergo a ^166^Ho scout dose procedure in the morning and a therapeutic procedure in the afternoon. The ARC will be randomly allocated to the left/right hepatic artery, and a standard microcatheter will be used in the contralateral artery. SPECT/CT imaging will be performed for quantitative analyses of the microsphere distribution directly after the scout and treatment procedure. Baseline and follow-up investigations include ^18^F-FDG-PET + liver CT, clinical and laboratory examinations. The primary endpoint is the comparison of tumor to non-tumor (T/N) activity ratio in both groups. Secondary endpoints include comparisons of mean absorbed dose in tumors and healthy liver tissue, infusion efficiency, the predictive value of ^166^Ho scout dose for tumor response. In the entire cohort, a dose-response relationship, clinical toxicity, and overall survival will be assessed. The sample was determined for the expectation that the ARC will increase the T/N ratio by 25 % (mean T/N ratio 2.0 vs. 1.6).

**Discussion:**

The SIM trial is a within-patient RCT that will assess whether ^166^Ho RE treatment can be optimized by using an ARC.

**Trial registration:**

The SIM trial is registered at clinicaltrials.gov (NCT02208804). Registered on 31 July 2014.

**Electronic supplementary material:**

The online version of this article (doi:10.1186/s13063-016-1643-3) contains supplementary material, which is available to authorized users.

## Background

Hepatic radioembolization (RE) has evolved to a standard-of-care therapy for patients with irresectable and chemorefractory colorectal cancer liver metastases (CRLM). During this treatment, radioactive microspheres are injected in the hepatic arteries to irradiate liver tumors from within, leading to local disease control [1]. However, treatment efficacy and predictability of the treatment effect can still be optimized, since the radiation dose to individual tumors is often inadequate and this cannot be predicted beforehand due to the lack of a reliable surrogate particle (scout dose) for routinely used yttrium-90 (^90^Y) microspheres [2].

Holmium-166 (^166^Ho) microspheres have been developed and clinically validated as a new microsphere for RE [3]. Besides β-radiation, these microspheres also emit low-energy γ-radiation and have paramagnetic characteristics, allowing for visualization and quantitative assessment of the microsphere distribution on single-photon emission computed tomography (SPECT) and magnetic resonance imaging (MRI) [4]. Furthermore, identical ^166^Ho microspheres can be administered as a scout dose to predict the distribution of the therapeutic microspheres [3, 5].

Another promising development is the availability of an anti-reflux catheter (ARC, Surefire Infusion System, Surefire Medical Inc., Westminster, CO, USA), aiming to increase the infusion efficiency and safety, by prevention of reflux [6–8]. The effects on hemodynamics induced by this catheter may improve the microsphere uptake ratio between tumorous and non-tumorous liver tissue (T/N ratio). The expanded catheter tip decreases blood pressure downstream of the tip, which is believed to lower the resistance that injected microspheres need to overcome in order to reach the tumor vasculature [9]. Furthermore, the catheter tip converts blood flow from a laminar into a turbulent pattern, which reduces the chance of missing a target branch by proper mixing of the microspheres in the vascular compartment. In addition, the catheter is fixed into a centro-luminal catheter position during infusion which may further increase the accuracy of the ^166^Ho scout dose as a predictor for the therapeutic ^166^Ho microspheres distribution [2].

In this article, we describe the study protocol of a prospective, comparative, clinical trial with the aim to investigate whether the ARC can be used to improve tumor targeting as well as the predictability of the treatment effect during ^166^Ho RE.

## Methods

### Hypothesis

We hypothesize that the use of the ARC increases the posttreatment T/N activity ratio and improves the predictive value of ^166^Ho scout dose distribution, in comparison with the use of a standard microcatheter (SMC).

### Study design

The SIM trial is a single-center, open-label, phase II, within-patient randomized controlled trial (RCT). As opposed to a conventional RCT design, patients act as their own controls; liver lobes (right versus left lobe) are the experimental units in this study. Patients with bilateral, irresectable, chemorefractory, liver-dominant CRLM will undergo two sequential procedures on the same day, during which a scout dose and a therapy dose of ^166^Ho microspheres will be administered in the left and right hepatic artery. These separate injections can be regarded as two separate treatments of functionally independent liver lobes. The use of the ARC will be randomly allocated (1:1) to the left or right functional liver lobe and a standard microcatheter (SMC) will be used in the contralateral side. The same catheter type will be used on the same side during the scout and therapy procedures.

This trial will be conducted in accordance with the principles outlined in the Declaration of Helsinki and will follow the Consolidated Standards of Reporting Trials (CONSORT) statement [10]. A Standard Protocol Items: Recommendations for Interventional Trials (SPIRIT) checklist is provided in Additional file 1 [11].

### Study population

All patients with irresectable, chemorefractory, and liver-dominant CRLM are eligible for participation in this trial if they meet the following inclusion criteria: histopathologically confirmed diagnosis of adenocarcinoma of the colon or rectum, hepatic metastases with measurable morphological appearance (≥1 cm) on cross-sectional imaging located in both the right and left hepatic arterial perfusion territory, irresectable and liver-dominant disease (i.e., pathological locoregional lymph nodes and up to five lung lesions < 1 cm are accepted), progressive disease after standard second-line systemic treatment or no further systemic treatment options due to severe side effects or unwillingness of the patient, age ≥ 18 years. Adequate follow-up must be logistically feasible and written informed consent must be obtained before enrollment in the study.

Exclusion criteria are: World Health Organization (WHO) performance score > 2, inadequate bone marrow function (hemoglobin < 6.0 mmol/l, leukocyte count < 3.0 × 10^9^/l, platelet count < 75 × 10^9^/l), inadequate liver function (bilirubin > 35 μmol/l, aspartate aminotransferase/alanine aminotransferase > 5 × upper limit of normal) or inadequate renal function (creatinine > 1.5 × upper limit of normal), prior hemihepatectomy, compromised biliary system (biliary stent or hepaticojejunostomy), Child-Pugh score B7 or worse, active hepatitis B or C, main portal vein thrombosis or previous portal vein embolization, severe celiac axis stenosis, unsuitable hepatic arterial anatomy, treatment with systemic chemotherapy within 4 weeks prior to RE, previous participation in a study classified as class III by a radiation safety committee, bleeding diathesis, pregnancy or breast feeding, or any condition that prevents safe treatment with RE.

### Investigations and interventions

The flowchart in Fig. 1 shows how the investigations and interventions in the SIM trial compare to standard radioembolization practice with ^90^Y microspheres.

**Fig. 1 Fig1:**
[figure not shown]
Flowchart of the investigations and interventions in the SIM trial. The study procedures are compared to standard radioembolization practice with yttrium-90 (^90^Y) microspheres. Note that in the SIM trial, the same particle is used during the scout and therapy procedure, and patients receive all procedures on the same day

#### Baseline investigations

Patients will first undergo pretreatment investigations as part of our routine RE workup: whole-body ^18^F-fluorodeoxyglucose positron emission tomography/computed tomography (^18^F-FDG-PET/CT) to rule out extensive extrahepatic metastases and calculate metabolic tumor burden; dual-phase (arterial + portal phase) liver CT to rule out other contraindications for RE, localize the liver tumors, and assess the hepatic arterial anatomy; laboratory investigations and a physical examination to assess vital functions and general condition of the patient.

#### Treatment planning

Eligible patients will be asked to provide informed consent to participate in the study. Next, the interventional radiologist and nuclear medicine physician will make an individualized treatment plan (including identification of the target vessels for selective infusion, identification of extrahepatic branches, and determining the need for coil embolization), based on the anatomy of the hepatic arterial vasculature visualized on pretreatment CT images. In all procedures, two selective injection positions (in the left and right hepatic artery) will be used to treat the whole liver on the same day. In patients with a variant hepatic arterial configuration, intrahepatic arterial branches (for example, the segment 4 artery) may be coil embolized to induce redistribution of blood flow through intrahepatic collaterals, and enable the use of two selective injection positions.

The total amount of ^166^Ho activity (A_Ho166_) required to deliver a whole liver absorbed dose of 60 Gy – the maximum tolerable radiation dose previously determined in a phase I dose-escalation study – is calculated using the formula:$$ {A}_{Ho166}(MBq)=\frac{60\;(Gy)}{15.87\;x\;{10}^{-3}\;\left(J/ MBq\right)}\;x\; Liver\; weight\;(Kg) $$Liver weight (in Kg) is determined by multiplying the volume of the liver (measurement based on CT) with the density of liver tissue (1.06 g/cm^3^). The scout procedure always consist of 250 MBq in 60 mg of microspheres (density 1.4 g/cm^3^), this activity is subtracted from the activity given in the treatment procedure. The treatment activity for each perfusion territory is fractionated based on its liver volume. If coil embolization of an intrahepatic branch is planned, the volume of its perfusion territory is included in the side that is anticipated to take over the blood supply.

#### Scout and therapy procedures

All patients will be admitted to hospital (University Medical Center Utrecht, The Netherlands) and will undergo a ^166^Ho scout procedure the next morning, followed by the ^166^Ho therapeutic procedure in the afternoon when the scout procedure was performed successfully.

During the ^166^Ho scout procedure, digital subtraction angiography (DSA) and C-arm CT imaging will be performed to confirm adequacy of the intended injection position(s), and rule out potential extrahepatic shunting. Coil embolization of side branches will only be performed when inevitable to warrant safe treatment. Nitroglycerine 200 μg is given per intra-arterial catheter to prevent vasospasm. Ultimately, a scout dose (250 MBq) of ^166^Ho microspheres will be administered through the anti-reflux catheter (ARC) and the SMC in the target vessels.

Next, a SPECT scan combined with a portal venous phase liver CT will be acquired and evaluated to rule out extrahepatic deposition of ^166^Ho microspheres, assess the intrahepatic biodistribution, as well as the liver-to-lung shunt. In the absence of extrahepatic deposition and a significant liver-to-lung shunt (visible accumulation ^166^Ho in the lung parenchyma), patients will undergo the therapeutic procedure in the afternoon. In the case of an unsuccessful scout procedure, the patient will be scheduled for a repeat procedure if possible.

During the therapeutic procedure, the calculated treatment activity of ^166^Ho microspheres will be administered in the same position(s) as during the scout procedure. Patients are discharged the day after treatment. The posttreatment SPECT (combined with a dual-phase liver CT) is obtained approximately 5 days after treatment to reduce the influence of detector dead time.

#### Follow-up investigations

A telephonic consultation will be scheduled at 2 weeks after treatment to evaluate the patient’s general condition, and ask for the occurrence of adverse events. One month after treatment, patients will undergo a physical examination and laboratory investigations for toxicity assessment. At 3-month follow-up, this is complemented by a whole-body ^18^F-FDG-PET + dual-phase liver CT for tumor response assessment, after which the study follow-up is completed.

### Study objectives

The primary objective is to assess the difference in posttreatment T/N activity ratio on SPECT/CT between administration with the ARC and SMC.

Secondary objectives include comparison of the following endpoints between administrations with the ARC and SMC: mean tumor and healthy liver absorbed dose on SPECT/CT, percentage of calculated treatment activity administered (infusion efficiency), predictive value of the ^166^Ho scout dose distribution, and posttreatment tumor response. Furthermore, the presence of a dose-response relation between tumor absorbed dose and posttreatment tumor response will be evaluated.

### Outcome assessment

In every target vessels’ perfusion territory, the absorbed dose on ^166^Ho-SPECT reconstructions will be determined for the metastases and the healthy liver tissue [4]. Consequently, a posttreatment T/N activity ratio will be calculated for each perfusion territory by dividing the number of counts in tumorous and healthy liver tissue.

The predictive value of the scout dose will be assessed by comparison of the distribution of the scout dose with the treatment dose. The analysis will be based on tumor and healthy liver absorbed doses on SPECT/CT analysis.

Infusion efficiency is defined as the percentage of the prepared treatment activity that is infused. The ^166^Ho activity that is not infused will be determined by measuring the administration system (vial, lines, and catheters) with a dose calibrator.

Response analysis will be performed in accordance with the Response Evaluation Criteria in Solid Tumors (RECIST) version 1.1 [12], for each functional liver lobe separately. Disease control rates (percentage of liver lobes with complete response, partial response or stable disease) will be determined by CT evaluation at 3 months posttreatment. Metabolic tumor response will be determined by assessing the change (relative to baseline) in total lesion glycolysis values on ^18^F-FDG-PET imaging. During the response assessment, observers will be blinded for the catheter type used.

The relationship between tumor absorbed dose on SPECT/CT and tumor response on both CT and ^18^F-FDG-PET will be characterized on the level of perfusion territories.

Common Terminology Criteria for Adverse Events v 4.03 will be used to describe laboratory and clinical toxicity for the entire cohort, with specific attention for device-related adverse events per catheter type such as the occurrence of reflux, vasospasm, or arterial dissections.

The municipal administration will be consulted to assess the overall survival, measured from treatment onward.

### Statistical considerations

#### Sample size calculation

A subgroup analysis of the T/N activity ratios in seven patients with CRLM, previously treated with ^166^Ho RE using a SMC [3], showed a mean T/N ratio of 1.6 (standard deviation 0.57). Sample size calculation, based on a two-sided paired *t* test for the comparison of T/N activity concentration ratios at an alpha level of 0.05 and power of 0.90, showed that at least 23 patients need to be included to detect a difference of 0.4 in mean T/N ratios (with an estimated standard deviation 0.57) in the ARC arm (estimated mean T/N ratio 2.0) and SMC arm (estimated mean T/N ratio 1.6). This corresponds to a 25 % increase (considered clinically relevant) in favor of the ARC arm. A rounded number of 25 patients will therefore be treated in this trial. Sample size calculations were performed with the computer program ‘PS: Power and Sample Size Calculation’ version 3.0 for MacOsX.

#### Randomization

A computer-generated stratified permuted block randomization with varying block sizes will be used. Difference in tumor burden (<10 % or ≥ 10 %) between the two target volumes in the liver will be used as stratification factors to eliminate the potential influence of tumor burden on the comparison of T/N activity ratios between catheter types.

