#### Statistical analysis

A comparison of continuous outcome measures between ARC and SMC infusions, such as the mean T/N activity concentration and mean decrease in total lesion glycolysis at 3 months posttreatment, will be performed by means of a paired *t* test. Categorical outcome measures, such as infusion efficiency and disease control rates at 3 months posttreatment, will be compared with a McNemar’s test. The value of the ^166^Ho scout dose distribution will be assessed per catheter type. Correlation and agreement with the ^166^Ho therapy dose distribution will be evaluated with a linear regression analysis (R^2^) and Bland-Altman analysis (limits of agreement), respectively. The dose-response relationship will be evaluated by linear regression analysis. Survival analysis by the Kaplan-Meier method will be used to estimate the median overall survival time for the entire cohort. The primary analyses will be performed on an intention-to-treat (as randomized) basis.

A two-sided *p* value < 0.05 will be considered statistically significant.

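### Stratifying left/right allocation by the unsigned burden difference does not ensure burden balance between catheters, and the paired t test does not adjust for it, so the influence of burden is not eliminated

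*Protocol article*

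**What the plan says.** Under Study design, the ARC "will be randomly allocated (1:1) to the left or right functional liver lobe", with the standard microcatheter (SMC) on the other side. Under Randomization: "A computer-generated stratified permuted block randomization with varying block sizes will be used". The stratification factor is the difference in tumor burden, in two levels (below 10%, or 10% and above), "between the two target volumes in the liver will be used as stratification factors". The stated purpose is "to eliminate the potential influence of tumor burden on the comparison of T/N activity ratios between catheter types". No text says that the difference carries a sign, or that allocation is to the higher- or lower-burden lobe.

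Under Statistical analysis, the comparison of continuous outcomes, including the T/N ratio, "will be performed by means of a paired" t test. No term for burden, stratum or side is named. The sample size is likewise "based on a two-sided paired" t test, "at an alpha level of 0.05 and power of 0.90", for a difference of 0.4 with SD 0.57. It gives 23 patients, rounded to 25.

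**The concern.** In a within-patient comparison, both lobes of a patient sit in the same stratum, so the stratum itself cannot confound the contrast. What can shift the ARC-minus-SMC difference is how often the ARC lands on the lobe with more tumor. Blocks within a size stratum balance ARC-left against ARC-right. They do not by themselves balance ARC-on-higher-burden against ARC-on-lower-burden. The plan treats burden as potentially relevant to the T/N ratio, since it stratifies on it, but neither the blocks nor the analysis takes account of its direction.

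At stake are a chance shift in the estimate from 25 pairs, power lost to variation that could be modelled, and a claim about the design that the trial report may repeat.

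**Working it through.** **The plan's own figure.** With difference 0.4, SD 0.57 of the paired difference, two-sided alpha 0.05 and power 0.90, the normal approximation is ((1.960 + 1.282) × 0.57 / 0.4)² = 21.3, or 23.3 after adding 1.960²/2. The noncentral t distribution gives power 0.895 at n = 23, 0.908 at n = 24 and 0.920 at n = 25. The stated 23 is thus reproduced to within one patient. The standard error at n = 25 is 0.57/√25 = 0.114.

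**What the blocks balance.** A simulation of 25 patients assumed half in each size stratum and block sizes 2 and 4; neither is in the article. The table gives the mean absolute imbalance in the upper stratum, that is, the number of patients with the ARC on the higher-burden lobe minus the number with the SMC on it.

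| Higher-burden lobe on the same side in | Strata as written | Simple randomization | Strata by size and direction |
|---|---|---|---|
| 50% of patients | 2.8 | 2.8 | 0.9 |
| 70% | 2.6 | 2.8 | 0.9 |
| 85% | 2.0 | 2.8 | 0.9 |
| 100% | 0.6 | 2.8 | 0.6 |

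With direction unrelated to side, the strata as written do no better than no stratification. They help only to the extent that the higher-burden lobe is mostly on one side, and the article does not say how often it is.

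**Size of the chance imbalance.** Assume that 12 of 25 patients are in the upper stratum, that direction is 50/50, and that the T/N ratio differs by g between higher- and lower-burden lobes in that stratum. None of these is in the article.

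- Let k be the number of these patients with the ARC on the higher-burden lobe, Binomial(12, 0.5). P(k ≥ 8) = 794/4096 = 0.19, so 8:4 or worse in either direction has probability 0.39. P(k ≥ 9) = 299/4096 = 0.07, or 0.15 in either direction.
- Shift of the estimate = g × (2k − 12)/25. For k = 8 this is 0.16g: 0.04 at g = 0.25 and 0.08 at g = 0.5, or 10% to 20% of the 0.4 target. For k = 9 it is 0.24g: 0.06 to 0.12.

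**Precision and power.** Take 0.57 as the residual SD, that is, excluding burden. The variance of the paired difference is then 0.57² + (12/25)g².

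- g = 0.25: 0.3249 + 0.0300 = 0.3549, SD 0.596, standard error 0.119.
- g = 0.5: 0.3249 + 0.1200 = 0.4449, SD 0.667, standard error 0.133.

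Simulated power for a true difference of 0.4:

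| g | Plain paired t test | Adjusted |
|---|---|---|
| 0 | 92% | 90% |
| 0.25 | 90% | about 91% |
| 0.5 | 82% | about 91% |

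The adjusted figures for g = 0.25 and 0.5 have signed burden in the model; adding side as well leaves power at 90% to 91%.

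**Validity.** The mean bias was about 0 in every simulated setting. The type I error of the plain test was at or below about 5.5% in all of them, and 5.0% with g = 0.5 and 12 of 25 patients.

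**The case against.** A reader might infer that the primary comparison is biased or its test invalid. The documents do not support that. Allocation is random, so burden is balanced in expectation, and burden variation enters the SD of the paired differences and hence the standard error. A shift of 0.08 is about 0.7 of the nominal standard error of 0.114, which is ordinary sampling error in a small trial. This stands.

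A reader might also infer that the scheme can never balance burden. That is too strong, as the table shows: if the higher-burden lobe were nearly always on one side, left/right blocks would balance it incidentally. This also stands; the scheme does not ensure balance.

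The sizes rest on assumptions. The article never quantifies an effect of burden on the T/N ratio, and the 39% counts imbalance in either direction; against one given catheter it is 19%. If 0.57 already includes burden variation, the plain test keeps its planned power and adjustment only adds to it.

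The missing side term is a weak point on its own. The blocks balance side, so it cannot distort the estimate systematically and costs precision at most. With an assumed left-right difference of 0.4 on top of a residual SD of 0.57, the plain test has 86% power against 92% adjusted for side. If 0.57 already includes side variation, the plain test has 98% or more.

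Finally, an adjusted analysis may exist in a full protocol or analysis plan that is not shown. That would help the analysis, but it would not make the statement under Randomization true of the design. Reading the factor as signed would not rescue it fully either, because one level would still mix pairs with small and opposite differences.

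**Conclusion.** The point holds in a limited form. The two-level unsigned factor with left/right allocation does not ensure that burden is balanced between catheters, and the named paired t test adjusts for neither burden nor side. The claim to eliminate the influence of burden is therefore unsupported. The consequence is chance imbalance and lost precision; the planned test remains valid.

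How much is lost depends on figures that the article does not give: the share of patients in the upper stratum, how often the higher-burden lobe is on the same side, and the T/N gap. Over the assumed range the loss runs from about one power point at a gap of 0.25 to about nine at 0.5. It is smaller if the higher-burden lobe is mostly on one side, and nil relative to plan if 0.57 already contains burden variation. The change is worth making because the data are already held at randomization and the cost is small.

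**What to change.** Before the comparison is seen, pre-specify as the primary analysis a linear regression of the within-patient ARC-minus-SMC T/N difference on two terms: the signed baseline tumor-burden difference (ARC lobe minus SMC lobe, uncentred) and side (+1 for ARC right, −1 for ARC left). The intercept is then the catheter effect at equal burden, averaged equally over the two sides. Keep the unadjusted paired t test as a sensitivity analysis. Under Randomization, replace the word eliminate with reduce.

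The change uses the tumor burdens already assessed for stratification. It spends two degrees of freedom (22 residual instead of 24), which costs one to two points of power (92% to 90%) if neither factor matters. Recruitment was ongoing at submission and no interim analysis is planned, so it can be made without knowledge of the result. Leave the randomization list as it is: changing it during accrual would mix two allocation schemes in 25 patients, and the adjusted analysis makes that unnecessary.
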